# Rationale and design of the 2 by 2 factorial design GnG-trial: a randomized phase-III study to compare two schedules of gemtuzumab ozogamicin as adjunct to intensive induction therapy and to compare double-blinded intensive postremission therapy with or without glasdegib in older patients with newly diagnosed AML

**DOI:** 10.1186/s13063-021-05703-w

**Published:** 2021-11-03

**Keywords:** gemtuzumab ozogamicin, glasdegib, acute myeloid leukemia, measurable residual disease

## Abstract

**Background:**

Overall survival remains poor in older patients with acute myeloid leukemia (AML) with less than 10% being alive after 5 years. In recent studies, a significant improvement in event-free, relapse-free and overall survival was shown by adding gemtuzumab ozogamicin (GO), a humanized antibody-drug conjugate directed against CD33, to intensive induction therapy once or in a sequential dosing schedule. Glasdegib, the small-molecule inhibitor of smoothened (SMO), also showed improved overall survival in patients not eligible for intensive chemotherapy when combined with low-dose cytarabine compared to low-dose cytarabine alone. These findings warrant further investigations in the phase III GnG trial.

**Methods/Design:**

This is a randomized phase III trial with measurable residual disease (MRD) after induction therapy and event-free survival (EFS) as primary endpoints. The two research questions are addressed in a 2 by 2 factorial design. Patients age 60 years and older are upfront randomized 1:1 in one of the two induction arms: GO administered to intensive induction therapy on days 1,4, and 7 versus GO administered once on day 1 (GO-147 versus GO-1), and double-blinded 1:1 in one of the subsequent treatment arms glasdegib vs. placebo as adjunct to consolidation therapy and as single-agent maintenance therapy for six months. Chemotherapy backbone for induction therapy consists of standard 7 + 3 schedule with cytarabine 200 mg/m^2^ continuously days 1 to 7, daunorubicin 60 mg/m^2^ days 1, 2, and 3 and high-dose cytarabine (1 g/m^2^, bi-daily, days 1, 2, and 3) for consolidation therapy. Addressing two primary endpoints, MRD-negativity after induction therapy and event-free survival (EFS), 252 evaluable patients are needed to reject each of the two null hypotheses at a two-sided significance level of 2.5% with a power of at least 85%.

**Ethics and dissemination:**

Ethical approval and approvals from the local and federal competent authorities were granted. Trial results will be reported via peer-reviewed journals and presented at conferences and scientific meetings.

**Trial status:**

Protocol version: 1st version 20.10.2020, no amendments yet. Study initiation on February 16, 2021. First patient was recruited on April 1st.

**Trial registration:**

ClinicalTrials.govNCT04093505; EudraCT 2019-003913-32. Registered on October 30, 2018.

**Supplementary Information:**

The online version contains supplementary material available at 10.1186/s13063-021-05703-w.

## Background

Acute myeloid leukemia (AML) is predominantly a disease of older patients for whom the prognosis is still poor [1, 2]. Intensive induction chemotherapy, usually consisting of an anthracycline and cytarabine, induces remission in about 50% of older fit patients, but most of these patients relapse and still succumb to their disease. Disease-related factors such as the genetic profile of the disease predict resistance to current standard therapy [3]. In line, the proportion of patients with a high-risk disease profile according to European LeukemiaNet (ELN)-2017 risk classification [4] increases with older age to roughly one-quarter of patients 70 years or older [5]. Combination of an anthracycline with cytarabine remains the standard of care of intensive induction therapy in patients considered medically fit [1, 2, 4] and the proportion of patients receiving intensive chemotherapy even in older patients is high with 80% to 90% in 60- to 70-year-old patients and 50% to 75% in patients aged between 70 and 75 years [5]. For patients who achieve a complete remission (CR) after induction chemotherapy, post-remission therapy is required to prevent relapse. However, despite intensive consolidation therapy, overall survival in older (≥ 60 years) patients remains poor with less than 10% being alive after 5 years [6]. Beyond age, genetic abnormalities constitute the most influential prognostic factors for survival [7, 8]. This is reflected in the current World Health Organization (WHO) classification of myeloid neoplasms and acute leukemia [9].

Gemtuzumab ozogamicin (GO) is a humanized immunoglobulin G4 antibody (hP67.6) directed against CD33 and conjugated to the DNA toxin calicheamicin via a hydrolyzable linker. GO/CD33 complexes are internalized into lysosomes, releasing calicheamicin and promoting single and double-strand breaks hereby inducing cellular death [10]. GO initially received accelerated FDA approval in 2000 for the treatment of patients aged ≥60 years with CD33 positive AML in first relapse [10]. Thereafter, a phase 3 study (S0106) was conducted by the Southwest Oncology Group (SWOG) in untreated de novo AML patients, comparing daunorubicin/cytarabine (DA) with 45 mg/m^2^ daunorubicin plus GO 6 mg/m^2^ on day 4 versus DA alone with 60 mg/m^2^ daunorubicin. The GO arm showed higher induction mortality (5.5% vs. 1.4%), without improving CR or relapse-free survival [11]. Based on these negative results, GO was withdrawn from the market in 2010. Meanwhile, results from five additional randomized studies with GO as adjunct to intensive induction therapy are available: Groupe Ouest Est d’Etude des Leuce´ mies aigue¨s et Autres Maladies du Sang (GOELAMS) AML2006IR [12], Medical Research Council (MRC) AML15 [13] and ALFA-0701 [14, 15], National Cancer Research Institute (NCRI) AML16 [16], and German-Austrian Acute Myeloid Leukemia Study Group (AMLSG) 09-09 [17]. ALFA-0701 randomized 278 patients aged 50 to 70 years with untreated de novo AML to either DA (60 mg/m^2^ daunorubicin) alone or to the same in combination with a fractionated GO induction schedule (3 mg/m^2^ on days 1, 4, and 7) [14]. Although CR with or without platelet recovery and early deaths were similar, patients in the GO arm had significantly improved median event-free (19.6 vs. 11.9 months; *P*=0.00018) and overall survival (OS) (34 vs. 19.2 months; *P*=0.046). A subgroup analysis revealed that the clinical benefit is mainly restricted to patients with favorable and intermediate-risk karyotype [14]. A meta-analysis of 3.325 patients (aged 18–84) from 5 randomized studies investigating GO as adjunct to induction chemotherapy in untreated AML concluded that the addition of GO improved OS in patients without adverse cytogenetics [18]. Rates of sinusoidal obstruction syndrome (SOS), a side effect associated with GO treatment, and 30- and 60-day mortality were lower with 3 mg/m^2^ vs. 6 mg/m^2^ GO [19]. Out of the five studies included in the meta-analysis, Castaigne et al. was the only one reporting on fractionated GO in a dosage of 3 mg/m^2^ on days 1, 4, and 7 (GO-147) [14, 18]. Interestingly, the addition of GO to induction therapy did not lead to an improved CR rate but a significantly higher rate of patients being negative for measurable residual disease (MRD-negative, 7% versus 39% in the standard and experimental arm, respectively) [20]. In addition, treatment with fractionated GO-147 was associated with a significant survival benefit in the large meta-analysis in comparison to patients that did not receive GO (OR:0.24, 99% CI 0.07–0.85), while this difference could not be shown for treatment with single-dose GO-1 (3 mg/m^2^) (OR: 1.0, 99% CI 0.78–1.3). Importantly, non-relapse mortality was not increased in patients treated with GO [14]. A major concern for patients receiving GO is the risk of SOS, especially among patients who received allogeneic hematopoietic cell transplantation (allo-HCT) within the preceding three months [21]. Revised dosing schedules significantly lowered rates of SOS to expected levels in patients being GO-naive [14, 22, 23]. Thus, the randomized comparison of GO-147 versus GO-1 as adjunct to intensive induction therapy appears as a logical consequence in terms of safety and efficacy [24].

The efficacy of GO during consolidation therapy was evaluated in 2 trials assessing GO on a randomized basis. In the MRC AML15 trial, a total of 948 patients were assigned to receive or not receive GO as adjunct to first consolidation therapy [13]. There were no differences in cumulative incidence of relapse (GO 46% vs.no GO 51% p=0.20) or OS (p=0.9) between the two groups. In the study from the Hemato-Oncologie voor Volwassenen Nederland (HOVON) group, older patients, who achieved CR after intensive induction therapy were randomized to either 3 cycles of GO (6 mg/m^2^ every 4 weeks) (*n*=113) or no postremission therapy (*n*=119) [25]. There were no significant differences regarding OS (*p*=0.52) and disease-free survival (*p*=0.40) between both groups. Thus, to date, no randomized data are available supporting the addition of GO in consolidation therapy [24, 26].

In AML, cytotoxic chemotherapy can reduce tumor bulk but is less effective at targeting tumor-initiating cells. The key challenge has been to identify the molecular mechanisms maintaining and sustaining tumor-initiating cell activity, self-renewal and survival. The Hedgehog (Hh) signaling is critical in terminal cell differentiation during embryogenesis and is believed to play a key role in the development of human malignancies when aberrantly activated. In AML aberrant activation of the Hh signaling pathway has been shown to be implicated in the maintenance of leukemia stem cell populations in several model systems [27]. Glasdegib is a selective, small-molecule inhibitor of smoothened (SMO), a membrane protein that regulates the Hh pathway. In vivo treatment of AML cells with glasdegib attenuated the leukemia-initiation potential in a serial transplantation mouse model [28]. Comprehensive gene set enrichment analysis revealed that glasdegib modulates self-renewal signatures and cell cycle progression [29]. Clinical data have supported these encouraging results. In a phase I study, a maximally tolerated dose of 400 mg daily was established and in a phase II study the recommended dose was 100 mg daily [30, 31]. In a randomized phase 2 study in older patients not fit for intensive chemotherapy, the addition of glasdegib 100 mg daily to low-dose cytarabine resulted in a significantly higher CR rate and OS as compared to low-dose cytarabine alone [32]. Interestingly, the beneficial effect of glasdegib on OS was not restricted to patients achieving a CR, as the observed beneficial effect on OS was larger than that seen on the CR-rate supporting the leukemic stem cell targeting effect of glasedib [32].

Based on the compelling preclinical data and the results of the phase-I and randomized phase-II studies, it appears reasonable and clinically feasible to combine standard intensive consolidation therapy with glasdegib. In this manuscript, we describe the rationale, design, and dosing details of the GnG study (clinicaltrials.gov identifier, NCT04093505; EudraCT No, 2019-003913-32), a phase III study to compare two schedules of GO as adjunct to intensive induction therapy and to compare intensive postremission therapy with or without glasdegib in a double-blinded manner in older patients with newly diagnosed AML.

Primary objectives of the study are (i) to assess the clinical efficacy of sequential or one-dose GO as adjunct to intensive induction therapy and (ii) to assess the clinical efficacy of glasdegib added to consolidation therapy and as a single agent for 6 months’ maintenance therapy in older patients with newly diagnosed AML.

## Methods

### Design

The GnG study is a randomized phase III trial with MRD after induction therapy and event-free survival (EFS) as primary endpoints. The two research questions are addressed in a 2 by 2 factorial design. Patients are upfront randomized to one of the two induction schedules (GO-147 versus GO-1) and to glasdegib or placebo (double blinded) added to consolidation therapy and as single agent for 6 months’ maintenance therapy in a 1:1 ratio. The trial is designed to gain evidence of the anti-leukemic activity of GO and glasdegib in older patients with newly diagnosed AML.

### Study setting and randomization

In Germany, patients with newly diagnosed AML are usually referred to academic Hospitals. In this study, patients will be recruited in 25 academic centers registered in the Study Alliance Leukemia (SAL) group. Participating centers are contacted by study monitors and the medical coordinator monthly to promote patient recruitment. Furthermore, after protocol amendments or upon relevant updates during the study, a newsletter will be sent to all participating centers. Conferences with the participating centers of the SAL network are done regularly to share information regarding therapy responses and complications seen within the study. Expecting at least 5 eligible patients per year and center, approximately 2 years are required to recruit the intended number of patients.

Each patient having signed informed consent and meeting all inclusion criteria is registered in the electronic case report form (eCRF). Via eCRF a unique patient ID (PAT-ID) is assigned. Following registration, eligible patients are upfront randomized 1:1 to induction chemotherapy containing either fractionated GO treatment (GO-147) or one single dose of GO (GO-1) and again 1:1 either to glasdegib or placebo (double-blinded) as adjunct to consolidation therapy and as single-agent for 6-months of maintenance therapy. Following these randomizations, 63 patients shall be allocated to each arm. Randomization is stratified by assumingly important prognostic factors age (≤70 years vs. > 70 years) and Eastern Cooperative Oncology Group (ECOG) performance status (PS) (ECOG PS = 0 vs. ECOG PS > 0). Block randomization with varying block lengths is used and performed using the web tool www.randomizer.at, by which randomization for double-blind clinical trials can easily be handled. Patients withdrawn from the trial retain their identification codes. Patients have to provide written informed consent before any protocol-specific procedures are performed. Applicable regulatory requirements, Good Clinical Practice, and ethical principles from the Declaration of Helsinki are adhered to during the study.

### Post-randomization events

If MRD-negativity cannot be measured, the outcome will be imputed. Any-cause death before MRD measurement, will be regarded as MRD-positive. Dropouts (including lost-to-follow-up) are considered as censoring events. The dropout rate for the assessment of the short-term endpoint is assumed to be 3%. For the long-term endpoint EFS, a dropout rate of 5% is expected 2 years after randomization. Dropout times are assumed to be exponentially distributed.

### Withdrawal of patients

A patient must be withdrawn from the trial (i) at any time at the patient’s own request, (ii) after induction therapy if the patient fails to obtain CR/CRi, (iii) at any time if unacceptable toxicity necessitating cessation of treatment is observed, (iv) at any time if there are changes in the medical status of the patient that compromise the patient’s safety or if the investigator considers that the withdrawal is in the patient’s best interest, (v) in case of pregnancy, (vi) at any time if insufficient protocol compliance from the patient is observed, (vii) if the patient is lost to follow-up. Patients who meet criteria i) to vi) and agree with the continuation of follow-up will be followed according to the protocol (supplementary Table 5.).

Unresolved AEs are followed in such cases; however, if the patient withdraws from the trial and also from consent for disclosure of future information (e.g., follow-up visits), further data collection is prohibited.

### Treatments and study procedures

#### Induction therapy

Patients receive one cycle of backbone induction therapy with standard 7 + 3 regimen: cytarabine 200 mg/m^2^ administered via continuous intravenous (IV) infusion for a total of 7 days and daunorubicin 60 mg/m^2^ days 1, 2, and 3. Patients are randomized to receive in addition GO 3 mg/m^2^ IV over 1 h (Mylotarg®), either on days 1,4, and 7 or only once on day 1 (GO-147 versus GO-1). Dose modification in case of CTC grade ≤2 toxicity is allowed in the GO-147 schedule to enable continued administration of GO on day 4 and day 7, respectively. In the case of grade 3 toxicity on day 1 and/or 4, patients will receive GO on days 4 and 7, respectively, if the CTC grade has improved to grade < 3 toxicity prior to infusion. In the case of CTC grade 4 toxicity, GO is discontinued. Likewise, patients who develop anaphylaxis, pulmonary edema, acute respiratory distress syndrome, or SOS after the first administration are not allowed to receive further doses of GO. On days 15 and 28 (window day 28 to day 42), a bone marrow aspirate specimen is collected for local and central assessment. If this bone marrow specimen is not evaluable for assessment of response, the bone marrow aspiration has to be repeated upon count recovery or day 42 whichever occurs first. In case of bone marrow blast count > 10% on day 15, or no CR or CR with incomplete neutrophil or platelet recovery (CRi) after induction therapy, one cycle of HAM (high dose cytarabine and mitoxantrone) as salvage therapy is allowed within the protocol.

#### Consolidation and maintenance therapy

During the consolidation phase, patients receive up to two cycles of cytarabine (1.0 g/m^2^) administered by IV infusion every 12 h on days 1, 2, and 3 [33]. Study drug (glasdegib 100 mg or placebo) is orally administered with approximately 8 ounces (240 mL) of water in the morning, at the same time each day from cycle day 1 to 28. Cycle 2 of consolidation chemotherapy is scheduled to start immediately after the end of cycle 1 or within the next two weeks if blood count recovery is delayed. In case of hematologic toxicity, a dose reduction or delay of glasdegib is not required. Remission status assessments take place after each consolidation therapy cycle. Patients may undergo allo-HCT after induction or after any of the consolidation therapy cycles.

During maintenance therapy, the dose of the study drug is the same as during consolidation therapy (glasdegib 100 mg). Maintenance therapy with glasdegib or placebo begins after the end of the 2nd consolidation therapy cycle (includes recovery period of up to 14 days, if applicable) and after assessment of remission status or 180 days after allogeneic HCT. Patients receive up to 6 cycles of 28 days each (168 days in total) within the maintenance schedule. Remission status assessments take place every three months for two years after beginning maintenance therapy. The overall treatment schedule is summarized in Fig. 1.

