**Fig. 1 Fig1:**
[figure not shown]
Overall treatment schedule GnG-Study. Abbreviations: DA, daunorubicin; low-dose cytarabine; GO, gemtuzumab ozogamicin; HiDAC, high-dose cytarabine (1 g/m^2^); MRD, measurable residual disease; CR, complete remission; CRi, CR with incomplete hematological recovery. In case of bone marrow blast count > 10% or no CR/CRi after on day 15 after induction therapy one cycle of HAM (high-dose cytarabine and mitoxantrone) is allowed. Maintenance is intended in all patients in CR/CRi irrespective of completion of consolidation therapy

Glasdegib and placebo are interrupted in patients experiencing adverse events of grade 3 or 4. Appropriate follow-up assessments are performed until adequate recovery from toxicity. In patients recovering within 21 days from dose interruption, glasdegib/placebo may be resumed. If hematological recovery parameters are not met after 21 days of dose interruption, permanent discontinuation of treatment with glasdegib/placebo is advised. Criteria for dose interruption and dose reductions in cases of non-hematological toxicities including applicable doses in milligrams are summarized in Tables 1 and 2.

**Table 1 Tab1:** Glasdegib interruptions in case of toxicities

Toxicity causing glasdegib interruption	Resumption within the first 21 days when:
Any toxicity grade ≥3 according to CTCAE criteria potentially attributable to glasdegib regardless of when it occurs in the cycle.	Toxicity returns to patient’s baseline/ toxicity resolved (non-hematological toxicity recovers to grade ≤1)
ANC < 0.1G/l and /or platelets <10G/l regardless of when it occurs in the cycle	ANC ≥0.1G/l and platelet count ≥10G/l and re-treatment can occur safely as per the investigator’s judgment
No resolution of above toxicities after 21 days	Discontinue medication permanently

Glasdegib doses omitted for toxicity are not replaced within that cycle (e.g., cycles are not to be prolonged beyond 28 days in order to make up for any missed glasdegib doses during that cycle). Toxicity is graded according to CTCAE criteria. Once the Glasdegib dose has been reduced, all subsequent cycles should be administered at that dose level, unless further dose reduction is required. Dose re-escalation is not allowed. Abbreviations: *CTCAE* Common Terminology Criteria for Adverse Events, *ANC* absolute neutrophil count.

**Table 2 Tab2:** Glasdegib dose reduction in case of non-hematological toxicities

Toxicity	Glasdegib dosage modification

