Non-hematologic toxicities grade ≥3 according to CTCAE criteria (excluding QTc prolongation, muscle spasms, and myalgias). First episode Second episode Third episode	Interrupt medication until toxicity recovers to grade ≤1, then: Dose level decrease 1 (DLD1): 75 mg DLD2: 50 mg Discontinue medication permanently
Renal toxicity, where serum creatinine or BUN are ≥2 × ULN or serum bicarbonate level is < 20 mmol/L. First episode Second episode Third episode	Interrupt medication until toxicity recovers tograde ≤1 then: DLD1 DLD2 Discontinue medication permanently
Electrocardiogram QT corrected (QTc) prolongation grade 1.	Continue at the same level.
QTc prolongation grade 2 and 3.	Interrupt and resume when QTc returns to ≤470 ms: - Within 7 days, dosing as before - Within 14 days, DLD1 Discontinue medication permanently, in case of no return to ≤470 ms after 14 days,
QTc prolongation grade 4 or repetitive grade 3 or grade 2 after DLD1.	Discontinue medication permanently

Toxicity is graded according to CTCAE criteria. Once the Glasdegib dose has been reduced, all subsequent cycles should be administered at that dose level, unless further dose reduction is required. Dose re-escalation is not allowed. Nausea, vomiting, or diarrhea must persist until next therapy cycle at grade ≥3 to require dose modification

Abbreviations: *CTCAE* Common Terminology Criteria for Adverse Events, *QTc* QT corrected, *DLD1* dose level decrease 1: 75 mg, *DLD2* dose level decrease 2: 50 mg, *ULN* upper limit normal

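### The study-drug rules for haematologic toxicity contradict each other: no delay required in the consolidation text, interruption and possible permanent stop in the text after Fig. 1 and in Table 1

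*Protocol article*

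**What the plan says.** All statements are in the protocol article, under Consolidation and maintenance therapy and in the text and tables that follow Fig. 1.

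- **Consolidation text:** "In case of hematologic toxicity, a dose reduction or delay of glasdegib is not required". This comes directly after the sentence that allows the second cycle to start up to two weeks late when count recovery is slow.
- **Text after Fig. 1, trigger:** "Glasdegib and placebo are interrupted in patients experiencing adverse events of grade 3 or 4". No exception is made for haematologic events, for phase or for cause.
- **Text after Fig. 1, time limit:** "If hematological recovery parameters are not met after 21 days of dose interruption, permanent discontinuation of treatment with glasdegib/placebo is advised".
- **Table 1, general row:** "Any toxicity grade ≥3 according to CTCAE criteria potentially attributable to glasdegib regardless of when it occurs in the cycle".
- **Table 1, low-count row:** "ANC < 0.1G/l and /or platelets <10G/l regardless of when it occurs in the cycle". Restart within 21 days requires both counts to be back at or above these thresholds, and the investigator to judge it safe.
- **Table 1, last row:** for "No resolution of above toxicities after 21 days" the instruction is permanent discontinuation.
- **Table 2, QTc rows:** grades 2 and 3 have their own limit, "Discontinue medication permanently, in case of no return to ≤470 ms after 14 days", and grade 4 leads directly to a permanent stop. The general non-haematologic row of Table 2 is marked "excluding QTc prolongation, muscle spasms, and myalgias".

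**The concern.** The first statement says that haematologic toxicity need not hold up study drug. The others hold it up for such toxicity and can end it permanently. The article does not say that one applies to consolidation and the others to maintenance, or that one overrides another.

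The conflict falls where low counts are most likely to matter. Study drug is given on days 1 to 28 of each consolidation cycle, alongside cytarabine on days 1 to 3, and the article itself provides for slow count recovery. Two things are at stake. One is consistent safety handling, including permanent discontinuation. The other is the exposure to glasdegib on which the EFS comparison rests.

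**Working it through.** No sample size, event count or power figure depends on this point, so there is no plan figure to reproduce. The check sets the rules side by side for a patient in a consolidation cycle. The article does not print CTCAE grade limits for blood counts, so grade is treated as given.

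| Situation | Consolidation text | Text after Fig. 1 | Table 1 |
|---|---|---|---|
| A. ANC below 0.1 G/l and/or platelets below 10 G/l | no delay required | interrupt, if graded 3 or 4 | interrupt |
| B. As A, not recovered after 21 days of interruption | no interruption was required | permanent stop advised | permanent stop |
| C. Other grade 3 or 4 cytopenia, possibly due to glasdegib | no delay required | interrupt | interrupt |
| D. Other grade 3 or 4 cytopenia, judged unrelated | no delay required | interrupt | not triggered |

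**Rows A and B.** The consolidation text and Table 1 give opposite answers, and in row B the difference is between continuing and stopping for good. The 21-day sentence after Fig. 1 also presupposes interruptions that wait for count recovery, which the consolidation text says are not needed.

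**Rows C and D.** The text after Fig. 1 gives the same answer in both rows, because it has no attribution condition. Table 1 gives different answers, because its general row has one. So even with the consolidation text set aside, the other two disagree in row D.

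**Planned days to which this can apply.**

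- Consolidation: up to 2 cycles × 28 days = 56 days.
- Maintenance: up to 6 cycles × 28 days = 168 days.
- Total: 56 + 168 = 224 days; consolidation share 56/224 = 25%.

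The 56 days are a ceiling for the consolidation phase. Under the low-count row an interruption lasts only until both counts are regained, so the days actually affected may be far fewer. A permanent stop during consolidation would also forfeit up to 168 maintenance days for a patient who would otherwise have gone on to them.

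**QTc prolongation, checked separately.**

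- Grade 2: only Table 2 applies, since Table 1 starts at grade 3. No conflict.
- Grade 3, recovering on days 15 to 21: permanently stopped under Table 2, but may resume on a literal reading of Table 1. The limits differ by 21 − 14 = 7 days.
- Grade 4, recovering within 21 days: permanently stopped under Table 2, but may resume on a literal reading of Table 1.

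The two grade 3 and 4 cases are overlaps between a general row and a specific one. Table 2 excludes QTc from its general row; Table 1 does not.

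**The case against.** The best defence is that the statements can be harmonised. The consolidation text says that a delay is not required; it does not forbid an interruption. Its position after the sentence on a late second cycle suggests that delay may refer to scheduling. Its remark on dose reduction agrees with Table 2, which reduces doses for non-haematologic toxicity only. The low-count row could be an exception for extreme values: its thresholds are one tenth of the remission thresholds in the Efficacy section (0.1 against 1.0 G/l for neutrophils, 10 against 100 G/l for platelets). The sentence after Fig. 1 could be a summary that the tables then refine.

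Each of these is possible, but none is stated. Table 1 applies its count rule at any time in the cycle, which weighs against the scheduling reading, and nothing confines Table 1 or the text before it to maintenance. The precedence remains open.

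It may also be said that an article condenses the full protocol. That excuses missing detail, but here the statements that are present disagree. It does limit the finding: Trial status names a protocol version that is not shown, and whether it has the same conflict is unknown.

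Four stronger readings are tempting, and the document does not support them.

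- **Two competing QTc limits, 14 and 21 days.** Table 2 has dedicated QTc rows, which would ordinarily override a general row. Only a missing exclusion in Table 1 remains.
- **Table 1 mislabelled as non-haematologic.** In the sentence that introduces the tables, the restriction to non-haematologic toxicity can attach to dose reductions alone, which fits the two table titles.
- **Nearly all patients interrupt under one rule and almost none under another, so the EFS contrast is diluted.** The article gives no rate, depth or duration of cytopenia, so neither step can be derived. The same rules apply to both blinded arms, and the primary analysis includes all randomised patients, so the validity of the comparison is not in question.
- **The 25 centres act differently.** The article shows inconsistent instructions. It does not show what sites do.

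**Conclusion.** The point holds for haematologic toxicity. The consolidation text cannot be reconciled, as written, with the text after Fig. 1 and the low-count row of Table 1. The text after Fig. 1 and Table 1 also differ on whether attribution to glasdegib is needed. Depending on the statement applied, the same patient with very low counts in consolidation continues, is interrupted or is permanently stopped.

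The effect on EFS, in either direction, cannot be sized from the document. The conclusion assumes only that the statements mean what they say and that no precedence rule exists in the text shown. The QTc overlap is a minor drafting gap for grade 3 or higher. No view is taken on which clinical rule is right.

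**What to change.** The sponsor should reconcile the consolidation text, the text after Fig. 1 and Table 1 into one rule set that states:

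1. which rule governs haematologic toxicity in consolidation and which in maintenance;
2. whether interruption for grade 3 or higher events requires possible attribution to glasdegib.

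As a minor addition, Table 1 should carry a cross-reference showing how its general row relates to the QTc rows of Table 2 for grade 3 or higher prolongation. The full protocol should be checked for the same wording. The clinical content is for the sponsor to settle.

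The cost is clarified wording, through the amendment route if the full protocol is affected, and a notice to sites. Study setting and randomization already foresees a newsletter to all centres after amendments or relevant updates. Sample size and the planned analysis are unchanged.
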